#### Acceptability via CASI Interview

Groups will be compared using two-sample t-tests if the outcome data follows a normal distribution. Despite the relatively small sample size (n=30 total, 15 per group) based on our past research into scale score comparisons conducted on a number of different products, we anticipate that meaningful differences in some scales may be detected in this study. For example, with respect to daily use activity scales in our previous study among a sample of 24 heterosexual couples, effect sizes resulting in significant differences in pair-wise comparisons of 3 different formulation conditions ranged from 0.60 (considered a medium effect size) to 2.67 (considered a very large effect size).

#### **14.7.5 Analysis Cohort**

The cohort will be defined as participants who are enrolled. It will be used for analyses of baseline characteristics, protocol deviations and violations, and trial conduct. The intent-to-treat cohort (ITT) will be defined as those who were enrolled, regardless of how many doses of drug were administered. Since the primary focus for this study is to estimate accurately the true rate of AE2 events, a modified ITT (mITT) group will be used for the primary analyses. This mITT group is defined as evaluable participants for the primary endpoint are described in [Section 14.2](#) for both Segment A and Segment B. The per protocol (PP) cohort is a subset of the evaluable cohort with subjects who meet all protocol specifications.

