## **10.8 ASSESSMENT OF PARTICIPANT STUDY PRODUCT ADHERENCE**

Dosing of Segment A participants will be performed by a study clinician. The first dose for Segment B will be placed by the participant in the clinic in the presence of a study clinician. Doses 2-7 for Segment B participants will be administered by participants at home, and adherence will be monitored by the use of MEMS cap devices (see Section 10.3 and 11.1.2.4). MEMS cap data will be used to determine which Segment B participants are sufficiently adherent to be evaluable (see Section 14.2) and will be included in the mITT (per protocol) analysis (see Section 14.7.5).

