### **13.4 UNEXPECTED MENSTRUAL LIKE BLEEDING**

In instances when unexpected menstrual like bleeding occurs, participants will be instructed to come to the study site for an evaluation. This unexpected bleeding will be considered an adverse event and appropriate clinical management will be based on exam findings.

Because every attempt will be made to enroll a participant into the study during the first two weeks of her menstrual cycle (Segment A) or first week of her menstrual cycle (Segment B), it is unlikely that a participant will menstruate during the period of product use. In the setting of menses or menses like bleeding that occurs during the week of product use, product use will be held and the PSRT consulted.

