### **13.6 PRODUCT HOLD**

Because of the short duration of both Segments of the study (single dose in Segment A, 7 daily doses in Segment B), product holds are not anticipated to be useful. Instead, participants with Grade 1 or 2 adverse events will be allowed to complete the exposure period for Segment B. For Grade 3 or 4 AEs, rather than product hold, product use will be discontinued permanently. In the unlikely event that a participant is intolerant of the study product immediately after placement, the site clinician will perform a pelvic exam and cervicovaginal lavage to remove all visible product.

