## 14.2 SAMPLE SIZE AND ACCRUAL

The primary aim of the study is to assess the local and systemic safety of one and seven day exposures to MB66. The primary endpoint is the proportion of participants who experience a Grade 2 or higher adverse event (AE) deemed related to study product. (The proposed total sample size is N=38 evaluable participants divided into Segment A (with n = 8 evaluable), and Segment B (with two arms, a MB66 arm and a placebo film arm, each with n = 15 evaluable). Evaluable participants (evaluable for the primary endpoint) in Segment A will be defined as participants who complete the Screening and Enrollment Visits and return for Visit 3. Evaluable participants in Segment B will be defined as participants who complete the Screening and Enrollment Visits and return for Visit 4 and use study product for at least 5 of the previous 7 days including the day before presentation (as assessed with MEMS cap data). Non-evaluable participants will be replaced, however, their data relevant to endpoints other than the primary endpoint will be preserved and used in tabulation and analysis of secondary and exploratory endpoints. In addition, if a participant becomes non-evaluable prior to the predefined visits described above, but experiences an AE during the time they were on study, their data will be included in the primary analyses as well. Based on previous studies of vaginal products conducted at the study site, the accrual of 38 evaluable subjects with normal reproductive tracts is expected to require the screening of approximately 70 participants and the enrollment of approximately 43 participants. The target for retention will be approximately 90% of enrolled participants over the 7-14-day follow-up period. Therefore, it is anticipated that 23 women exposed to active study drug in all arms (8 during Segment A and 15 during Segment B) will be evaluable. [Table 16](#) calculates the probability of events in Segment A participants (n=8) and [Table 17](#) calculates the probability of events in Segment B participants (n=15).

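### The primary AE2 analysis set is selected by adherence after randomisation and is stated in three inconsistent ways, so one woman can change the result of the 30% rule

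*Protocol*

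**What the plan says.** Four places in the protocol bear on who enters the primary AE2 analysis.

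- **Section 14.7.5** makes the mITT the primary set: "a modified ITT (mITT) group will be used for the primary analyses". It defines the set by reference to Section 14.2: "This mITT group is defined as evaluable participants for the primary endpoint are described in" that section. It also names an ITT cohort of all enrolled women whatever their dosing, but does not give that cohort the primary analysis.
- **Section 10.8** says "MEMS cap data will be used to determine which Segment B participants are sufficiently adherent to be evaluable" and ties mITT membership to this. It labels the mITT as per protocol, whereas Section 14.7.5 makes per protocol a narrower subset.
- **Section 14.2** defines a Segment B woman as evaluable if she completes screening and enrolment and goes on to "return for Visit 4 and use study product for at least 5 of the previous 7 days including the day before presentation". Non-evaluable women are replaced, and "their data relevant to endpoints other than the primary endpoint will be preserved". A later sentence makes an exception for a woman who becomes non-evaluable before the defining visit "but experiences an AE during the time they were on study, their data will be included in the primary analyses as well". The exception has no condition on grade or relatedness.
- **Section 14.7.2** states the decision rule: 30% is ruled out if at most one woman has an AE2, counted out of fifteen enrolled per arm.

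AEs can themselves lead to failing the film-use threshold. Section 13.6 says "For Grade 3 or 4 AEs, rather than product hold, product use will be discontinued permanently". Section 13.4 treats unexpected menses-like bleeding as an AE and says that, when it occurs in the dosing week, "product use will be held and the PSRT consulted".

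**The concern.** A safety estimate should cover the women who were exposed. Here membership is settled after randomisation and first dose, by returning for Visit 4 and by film use up to the day before. Tolerating the film makes a woman more likely to qualify.

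The text then allows two readings, and neither is sound.

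- **Evaluable women only** (Sections 14.7.5 and 10.8 as worded): an AE2 that leads a woman to stop film is left out, and another woman takes her place. The rate is biased downward.
- **With the Section 14.2 exception:** a non-evaluable woman enters because she had an AE, while an equally exposed non-evaluable woman without one does not. The rate is biased upward and n is no longer 15. The exception also reaches only women who become non-evaluable before the defining visit. A woman who stops film because of an AE but still attends Visit 4, as Sections 11.2.4 and 13.7.1 encourage, fails on adherence at that visit and is not clearly covered.

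The wording in Section 14.7.2 supplies a third denominator. At stake is the stated focus of the primary analysis: whether the AE2 upper bound falls below 30%.

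**Working it through.** **1. The plan's own figure.** The one-sided 95% Clopper-Pearson upper bound for x events in n is the 0.95 quantile of Beta(x+1, n−x). For 1/15 it is 27.9%, as Section 14.2 states. For 0/15 it is 18.1% and for 2/15 it is 36.3%. The rule of at most one event in 15 is therefore right when n is 15.

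**2. Likely numbers.** Section 14.2 targets about 90% retention. For 38 evaluable women, 38/0.90 = 42.2, so 43 enrolled, as stated. Per Segment B arm, 15/0.90 = 16.7, so about 17 enrolled. One or two women per arm with disputed inclusion is within the plan's own expectation.

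**3. One data set, three answers.** Take an arm with 17 exposed women: 15 evaluable with one AE2, and two non-evaluable, of whom one had an AE2 and the other no AE.

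| Set | AE2 / n | Upper bound | Below 30%? |
|---|---|---|---|
| Evaluable only | 1/15 | 27.9% | yes |
| Evaluable plus Section 14.2 exception | 2/16 | 34.4% | no |
| All exposed | 2/17 | 32.6% | no |

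Two events give 31.0% at n = 18 and first pass at n = 19 (29.6%). With no AE2 among the 15 and one in a disputed woman, every reading passes: 0/15 18.1%, 1/16 26.4%, 1/17 25.0%.

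**4. Downward bias if the exception is not applied.** Let r be the true AE2 rate and s the share of affected women who become non-evaluable and are replaced, with no loss among unaffected women. The rate among evaluable women is r(1−s)/(1−rs). The chance of meeting the rule is P(X ≤ 1) with n = 15.

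- r = 0.30, s = 0: rate 0.30, chance 3.5%.
- r = 0.30, s = 0.25: 0.225/0.925 = 0.243, chance 8.9%.

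The share s is an assumption. At s = 0.25 the loss is 0.30 × 0.25 = 7.5% of women, which fits within the roughly 10% planned loss.

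**5. Upward bias if the exception is applied.** Let d be the share of women non-evaluable, the same with and without an AE. If only AE2 women are restored, the rate reads as r/(r + (1−r)(1−d)).

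- r = 0.10, d = 0.10: 0.10/0.91 = 11.0%.
- r = 0.10, d = 0.20: 0.10/0.82 = 12.2%.

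These are maxima, because the exception restores a woman with an AE of any grade. If 30% of women had some AE (an assumption), the denominators become 0.30 + 0.70(1−d) = 0.93 and 0.86, and the readings are 10.8% and 11.6%.

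**The case against.** The strongest reply is that Section 14.7.5 does not define evaluability itself. It sends the reader to Section 14.2, where the exception sits. A specific exception following a general rule can be read as one rule, so a reader who infers a flat contradiction goes further than the text does. That stands. What remains is that the exception does not make these women evaluable, that Section 10.8 ties the mITT to adherence with no exception, and that Section 14.7.2 uses another denominator.

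A reader might also infer a large false-pass rate. With s at one half or three quarters, the formula in step 4 gives 23% or 57%. Those figures require the exception to be ignored, and they imply that 15% or 22.5% of all women are lost to AE2s alone, above the roughly 10% loss that the protocol plans. The documents do not support them.

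Nor is the 30% rule the trial's only safety decision, as a reader might suppose. Under Section 13.6, Grade 1 and 2 AEs do not require stopping film. Under Section 13.8, a related Grade 3 or higher AE meets the criteria to pause or stop enrolment, so it cannot pass unnoticed. The PSRT also decides on advancing to Segment B, and Section 8.1.1 has all AEs reviewed and analysed. These safeguards protect participants. They do not settle who is counted in the primary estimate.

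Finally, the example is narrow. One disputed woman changes the verdict only when the evaluable set has exactly one AE2, and in the example the exception and the all-exposed set agree. Both points are correct.

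**Conclusion.** The concern holds at should-fix level. The primary AE2 set is selected after randomisation, and Sections 10.8, 14.2, 14.7.2 and 14.7.5 do not give one rule for it. Importing the exception into Section 14.7.5 leaves inclusion dependent on outcome, though the bias is small and overstates risk: a true 10% reads as at most 11.0–12.2% with 10–20% non-evaluable. Not importing it understates risk: at a true 30%, the chance of wrongly ruling out 30% rises from 3.5% to about 9% if a quarter of affected women are dropped. That share is assumed. The verdict can change on one woman, from 27.9% to 34.4% or 32.6%, when the evaluable set has exactly one AE2. This is not detail left to the SAP that Section 14.7.2 announces, because the protocol itself fixes the set and states it inconsistently.

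**What to change.** Amend Sections 10.8, 14.2, 14.7.2 and 14.7.5 together.

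- Define one primary safety set: all women who received at least one film, analysed by film received, with the same rule for numerator and denominator.
- Replace the fixed rule of zero or one event in 15 by the Clopper-Pearson bound at the actual n (for example 1/17 gives 25.0% and 2/17 gives 32.6%).
- Delete the conditional-inclusion sentence in Section 14.2.
- Keep the evaluable set as a supportive analysis and for PK, and use one name for it in Sections 10.8 and 14.7.5.

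The replacement and randomisation scheme can stay as it is. No new data are needed, since Sections 11.2.4 and 13.7.1 already plan follow-up after film is stopped. The cost is wording, plus a few women with low exposure in the denominator, which the supportive evaluable-set analysis addresses.

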## **15. DATA HANDLING AND RECORD KEEPING**

### **15.1 DATA QUALITY ASSURANCE**

Site visits will be conducted to verify the qualifications of each Investigator, inspect the study center facilities, and inform the Investigators of their responsibilities and the procedures for ensuring adequate and correct documentation.

Investigator training will be held to introduce Investigators and their study staff to the clinical protocol, CRFs, study procedures, regulatory requirements, and use of the study assessments.

The Investigator is required to prepare and maintain adequate and accurate case histories designed to record all observations and other data pertinent to the study for each study participant. All information recorded on the CRFs for this study must be consistent with the participant's source documentation (i.e., medical records).

## **15.2 DIRECT ACCESS TO SOURCE DATA AND STUDY AUDITS**

Site monitors will perform onsite visits to review protocol compliance, compare CRFs and individual participant's source records, assess drug accountability, check for CRF completeness and clarity, and ensure that the study is being conducted according to pertinent regulatory requirements. CRF entries will be verified with source documentation. The review of medical records will be performed in a manner to ensure that participant confidentiality is maintained.

Representatives of the IRB, FDA, DAIDS, and/or the Sponsor may also wish to carry out such data checks during onsite audit inspections, including direct access to source data.

## **15.3 ARCHIVING STUDY RECORDS**

Study documentation must be retained for a minimum of 2 years after the last approval of a marketing application and until there are no pending or contemplated marketing applications or until at least 2 years have elapsed since the formal discontinuation of clinical development of the investigational product. However, these documents may be retained for a longer period if required by the applicable legal requirements.

The investigator will maintain, and store securely, complete, accurate and current study records throughout the study. Study records will not be destroyed prior to receiving approval for record destruction from DAIDS. Applicable records include source documents, site registration documents and reports, correspondence, informed consent forms, and notations of all contacts with the participant.

## **16. CLINICAL SITE MONITORING**

Study monitoring will be carried out by Pharmaceutical Product Development Inc., which will perform this function under contract to DAIDS (PPD, Wilmington, NC). Site monitoring visits will be conducted to assess overall study compliance, as required per Requirements for On-Site Monitoring of DAIDS Funded and/or Sponsored Clinical Trials, GCP, and FDA regulations 21 CFR Part 312:

[http://www.niaid.nih.gov/LabsAndResources/resources/DAIDSClinRsrch/Documents/onsitemonitor\\_reqs.pdf](http://www.niaid.nih.gov/LabsAndResources/resources/DAIDSClinRsrch/Documents/onsitemonitor_reqs.pdf)

Study monitors will visit the site to complete the following:

- Assess compliance with the study protocol, Good Clinical Practices (GCP) guidelines, and applicable regulatory requirements, including US CFR Title 45 Part 46 and Title 21 Parts 50, 56, and 312
- Review informed consent forms, procedures, and documentation
- Perform source document verification to ensure the accuracy and completeness of study data
- Verify proper collection and storage of biological specimens

- Verify proper storage, dispensing, and accountability for investigational study products
- Assess implementation and documentation of internal site quality management procedures
- Assess site staff training needs

Site investigators will allow study monitors to inspect study facilities and documentation (e.g., informed consent forms, clinic and laboratory records, other source documents, case report forms), as well as observe the performance of study procedures. Investigators also will allow inspection of all study-related documentation by authorized representatives of the DAIDS, Sponsor and US regulatory authorities. A site visit log will be maintained at the study sites to document all visits. The outcomes of the monitoring visits and the subsequent reports of resolutions of any identified problems will be provided to the Sponsor of the IND application, and also submitted to DAIDS Clinical Operations.

## **17. HUMAN SUBJECTS PROTECTION**

The investigators will make efforts to minimize risks of these products to human subjects. Participants will take part in a thorough informed consent process throughout their participation in the study. Before beginning the study, the investigators will have obtained IRB approval and the protocol will have been submitted to the FDA. The investigators will permit audits by the NIH or the FDA or any of their appointed agents.

### **17.1 INSTITUTIONAL REVIEW BOARD/ETHICS COMMITTEE**

IRB continuing review and approval will be obtained from the reviewing EC/IRB at least once per year. If IRB approval expires (e.g., lapse in continuing review), all ongoing research activities will stop, unless the investigator determines that it is in the best interest of already-enrolled participants to continue their study-related activities. New participants will not be enrolled on the study until IRB approval to continue the research is obtained.

### **17.2 SPECIAL POPULATIONS**

Study staff will offer screening to eligible women of all ethnic and racial groups. Members of the study staff are not seeking the screening or enrollment of women in special or vulnerable populations. The following Section also discusses special considerations for male partners of participants.

#### **17.2.1 Men**

Men are not included as subjects in the study because the study is testing a vaginal application of the study product. The male sexual partners of women participating in this study will not be consented or monitored for several reasons. Protocol-specified guidelines for abstinence and condom use are expected to protect male partners from exposure to the study product.

### **17.2.2 Children**

The NIH has mandated that children be included in research trials when appropriate. This study will enroll women aged from 18 up to 21 who are able to give informed consent. This study meets "Justifications for Exclusion" criteria for younger children as set forth by the NIH. Specifically, "the research topic to be studied is irrelevant to (young) children" and "a separate, age-specific study in (adolescent) children is warranted and preferable" at a later time.

### **17.2.3 Prisoners**

Prisoners will not be included in this study (for screening or enrollment). Any participants incarcerated during the course of participation in the trial will not be followed during their incarceration, and will be discontinued from the study. Participants who have been released from incarceration will be permitted to return for any protocol specified follow-up or safety visits per the guidelines of the local IRB.

### **17.2.4 Pregnant women**

Pregnancy is an exclusion criterion because there is no current knowledge on the safety of the product during pregnancy; At the Screening Visit, a urine pregnancy test will be performed on all women. During the informed consent process, women will be informed that the study film is not known and not expected to prevent pregnancy and that the effect of the study film on a developing human fetus is not known. All enrolled participants will be required to be using a reliable method of contraception, such as hormonal contraception, intrauterine device or sterilization. Women who become pregnant during the study period following randomization and exposure to study product will not be excluded from analysis. Every effort will be made to maintain periodic contact with the participant after study termination until the completion of the pregnancy in order to determine the pregnancy outcome, and to obtain records from the facility at which the outcome occurred.

## **17.3 GOOD CLINICAL PRACTICE**

The procedures set out in this study protocol are designed to ensure that all relevant parties abide by the principles of the Good Clinical Practice (GCP) guidelines of the ICH, and will adhere to DAIDS policies. The study will also be carried out in keeping with local legal requirements.

## **17.4 INFORMED CONSENT**

Written informed consent will be obtained from all potential study participants at Visit 1, prior to the initiation of any study-related procedures. The informed consent process will give individuals all of the relevant information they need in order to decide whether to participate, or to continue participation, in this study. Potential research participants will be permitted to ask questions and to exchange information freely with the study investigators. Only listed study investigators may obtain informed consent from potential study participants. The investigators will keep research participants fully informed of any new information that could affect their willingness to continue study participation.

## **17.5 STORED SAMPLES**

### **17.6 SPECIMEN STORAGE AND POSSIBLE FUTURE RESEARCH TESTING**

Participants will be consented for future use of cervicovaginal lavage (CVL) specimens and blood samples. Any leftover CVL samples will be stored at the [name] Laboratory, and serum at LeafBio, Inc. for an indefinite period of time (addresses given in Section 3).

Any results from research done on leftover specimens will not be placed in health records and will be kept confidential. Informed consent will give participants the option to withdraw their consent for use of their specimens for future research. The language and format employed in the screening and enrollment consents for these purposes are an IRB-approved means commonly employed in studies performed at this and other study sites within our institution to obtain permission for use of stored samples. All primary study endpoints, protocol-specified testing, and QA/QC testing will be ascertained prior to any additional testing of stored specimens. When all laboratory assays have been completed and the study has been closed, the PI for the study will notify the [name] Laboratory and Mapp Laboratory Managers to discard all samples from participants in the study who chose to have their samples destroyed at the end of the study. These samples will be discarded in the appropriate manner and the disposition will be documented. The applicable NIH Data Sharing Policy (<http://gds.nih.gov/03policy2.html>) will be followed for data obtained from stored specimens.

